#### Metabolomics study analysis

A multivariate statistical analysis will be conducted from the data obtained from the MS or NMR spectra of collected blood or urine samples using SIMCA-P version 12.0 (Umetrics, Umeå, Sweden). A principal component analysis (PCA), partial least squares-discriminant analysis (PLS-DA), or orthogonal projections to latent structure-discriminant analysis (OPLS-DA) will be used to process the data. In addition, to investigate the variables affecting the differences in metabolites between the groups, the loading plot, S-plot, or the variable influence on projection (VIP) value will be used.

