##### Metabolomics

A metabolomics study will be performed to analyze the difference between (1) FD before and after acupuncture treatment and (2) the acupuncture and sham acupuncture groups. Blood and urine samples will be collected at baseline and after 4 weeks. After collecting the blood, the plasma will be isolated by centrifugation and stored in a −73 °C deep freezer. The urine samples will be inverted two or three times, pipetted into the cryo tubes, and stored in the deep freezer until the time of analysis. The sample will be analyzed by NMR and ultra-performance liquid chromatography quadrupole/time of flight mass spectrometry (UPLC-Q/TOF MS). After obtaining the NMR and MS data for blood and urine samples, the patterns and biomarkers for FD could be discovered using a multivariate statistical analysis.

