### Statistical analysis

A statistical analysis will be conducted by an independent statistician using SPSS 16.0 (SPSS Inc., Chicago, IL, USA). All continuous variables will be presented as means and SDs, and categorical variables will be shown as a number (%). All analyses will be based on the intention-to-treat principle using the last observation carried forward rule. The statistical significance level will be considered to be 0.05 (two-sided) with 95 % confidence intervals (CI). When continuous variables are compared between two groups, a two-sample *t*-test (parametric method) or Mann–Whitney *U* test (non-parametric method) will be used. The paired *t*-test (parametric method) or Wilcoxon signed ranks test (non-parametric method) will be used to compare continuous variables both before and after the treatment. When the variable is categorical, a chi-square test or Fisher’s exact test will be implemented. If there are statistically significant differences between groups, an analysis of covariance (ANCOVA) or logistic regression will be used.

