FD is classified into two subtypes: PDS and epigastric pain syndrome (EPS). Patients with PDS complain of bothersome fullness and abdominal discomfort after meals, while EPS focuses on an epigastric burning sensation that frequently occurs during fasting [17]. PDS is considered a more appropriate target subject than EPS in this trial because meal ingestion can aggravate PDS symptoms [55], and PDS patients can be more vulnerable to epigastric pressure due to abdominal hypersensitivity [56]. Another reason to choose PDS as a subject in this trial is the large proportion of PDS compared with other subtypes in Korea. Though more EPS patients are detected than PDS patients in the USA due to the tendency to overestimate gastroesophageal reflux diseases [57], more than 70 % of FD patients were designated to the PDS subtypes in Korea [3]. Our previous study [16] also found a more than 60 % PDS subtype ratio; therefore, PDS is considered to represent most FD patients in Korea.

The effect of acupuncture on the hypothalamus and its influence on the autonomic nervous system [58, 59] implies a homeostatic feature, which is thought to be closely related to a TKM perspective and focuses on systemic and holistic treatment. Therefore, metabolism studies are gaining attention in the field of acupuncture trials. One previous study showed the acupuncture effect of reversing the levels of metabolites affected in FD patients, such as leucine/isoleucine and lactate, so that they more closely resemble those of healthy controls [15]. However, this method had several defects, such as a small sample size (six subjects per group), the absence of a sham control, and only profiling polar metabolites by NMR. In the present study, we planned 35 subjects per group as a comparatively large sample, and the change and difference of metabolomic profiles will be investigated by H NMR and MS compared with the sham group.

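### The before/after acupuncture metabolomics contrast is paired, but the multivariate methods named for the spectra do not use the pairing in their standard form, so the model loses sensitivity and predictive performance for that contrast

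*Protocol article*

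**What the plan says.** The Metabolomics entry under Secondary outcomes lists two comparisons: "FD before and after acupuncture treatment and (2) the acupuncture and sham acupuncture groups". On sampling it says: "Blood and urine samples will be collected at baseline and after 4 weeks". Each participant can therefore give one pair of plasma samples and one pair of urine samples, and the first comparison is made within patients. The Discussion gives the number: "we planned 35 subjects per group as a comparatively large sample".

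The same entry expects that "the patterns and biomarkers for FD could be discovered using a multivariate statistical analysis". The section Metabolomics study analysis then names principal component analysis in SIMCA-P and continues: "partial least squares-discriminant analysis (PLS-DA), or orthogonal projections to latent structure-discriminant analysis (OPLS-DA) will be used to process the data". Loading plot, S-plot or VIP values follow, "to investigate the variables affecting the differences in metabolites between the groups". That section mentions no difference spectrum, no centring within person and no multilevel version of these methods.

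The parent section, Statistical analysis, does provide for pairing in general: a paired t-test or "Wilcoxon signed ranks test (non-parametric method) will be used to compare continuous variables both before and after the treatment".

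**The concern.** In their usual form, PCA, PLS-DA and OPLS-DA take a matrix with one row per spectrum. For a before/after contrast, the class label is the time point, and nothing tells the model that two rows come from one person. Diet, habitus and other stable personal differences then count as noise around the change of interest. OPLS-DA sets aside variation unrelated to the class, which helps interpretation, but it does not use person identity either.

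The plan samples each person twice, and the multivariate step as named does not use this. A model that contains a real change could then show a weak Q2 or accuracy and be set aside as unpredictive. The Discussion itself lists small sample size as a limitation, so sensitivity matters.

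**Working it through.** **The plan's own figure.** The documents state no sample size, correlation or effect size for metabolomics. The 35 per group comes from the responder outcome, with p_t = 0.70, p_c = 0.35 and mean 0.525:

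- 1.96 × √(2 × 0.525 × 0.475) = 1.384
- 0.8416 × √(0.70 × 0.30 + 0.35 × 0.65) = 0.557
- n = (1.384 + 0.557)² / 0.35² = 30.8, so 31 per group
- with 10% dropout, 31 / 0.9 = 34.4, so 35

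The figure is reproduced and is not disputed. It gives at most 35 pairs in the acupuncture arm.

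**Where the pairing matters.** Code before as −1 and after as +1. With complete pairs, the first PLS weight vector is proportional to the sum of y·x over all rows, which equals Σ(after_i − before_i).

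Now subtract each person's two-sample mean. The rows become −d_i/2 and +d_i/2, where d_i = after_i − before_i, and the sum is again Σd_i. Before any scaling, the first component therefore points the same way with or without the pairing. The scores differ. A raw score also carries the person's own level, which makes up a share ρ of each variable's variance, and centring removes it. So the loss should appear in prediction and hardly at all in the ranking of variables.

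**Illustration.** Only the 35 pairs come from the documents. These inputs are assumed: 200 variables, 10 of them shifted by 0.5 SD, ρ = 0.5, one component, and 7-fold cross-validation that keeps both samples of a person in one fold.

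| Data entering PLS-DA | Accuracy | Q2 |
|---|---|---|
| Raw spectra | about 0.66 | about 0.13 |
| Within-person data | about 0.80 | about 0.35 |

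The difference is 0.80 − 0.66 = 0.14 in accuracy and 0.35 − 0.13 = 0.22 in Q2. A separate run gave 0.65 and 0.76 for accuracy. Whether variables are scaled to unit variance moves the within-person value across about that range, 0.76 to 0.80. In that run, with no true change, both versions gave 0.50, so neither invents a signal. The true variables found among the top 10 were nearly the same (0.69 raw, 0.68 within person), as the algebra predicts.

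**Range over the unknown correlation** (two components, other settings as above, 100 runs each):

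| ρ | Q2 raw | Q2 within | Accuracy raw | Accuracy within |
|---|---|---|---|---|
| 0.3 | −0.03 | 0.19 | 0.61 | 0.69 |
| 0.5 | −0.04 | 0.27 | 0.64 | 0.73 |
| 0.7 | −0.02 | 0.43 | 0.67 | 0.84 |
| 0.9 | −0.17 | 0.66 | 0.71 | 0.97 |

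The direction is the same throughout, and the gap widens as ρ rises. One caution: the within-person model places a sample with the help of that person's other sample, while the raw model places it alone. The gap measures the value of the pairing. It does not show that the raw model picks the wrong metabolites.

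**The case against.** The strongest reply is that the article condenses a fuller protocol. It names model families and does not say what enters them. Subtracting a person's mean is preprocessing and could be set out elsewhere. The third aim under Objectives and the Discussion both speak of changes in metabolites, so the authors have change in mind. This has weight: the article nowhere says that the samples will be treated as independent. What remains is that it defines a paired contrast, gives the spectra their own methods section, and names there only methods whose standard form ignores pairing. An analyst who follows that section as written would not use the pairs.

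Three stronger readings are tempting and are not supported:

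- A reader might infer that single metabolites will be compared before and after with an unpaired test, at a large cost in power. The plan specifies no such test. Statistical analysis assigns paired tests to before/after comparisons of continuous variables, and the metabolomics section sits under it without revoking them.
- A reader might infer that cross-validation will push predictions below chance. In the illustration, leaving out single spectra gives accuracy of about 0.30 on raw data, because a person's other sample stays in the training set with the opposite label. The document states no cross-validation scheme, so this is a trap to avoid and not a fault in the plan.
- A reader might infer that the change would be missed altogether. With whole-person folds, raw accuracy of about 0.66 is still above the 0.50 expected with no effect. The signal is weakened but remains visible.

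It is also fair to say that this contrast is exploratory and within one arm. The Background states the metabolomics purpose as acupuncture compared with sham.

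**Conclusion.** The point holds as a loss of sensitivity and predictive performance in one exploratory multivariate analysis. Under the assumed values, accuracy falls from about 0.80 to 0.66 and Q2 from about 0.35 to 0.13. The size depends on the within-person correlation, the size of the shift and the number of variables, none of which the documents give. The ranking of metabolites is nearly unchanged and false positives are not inflated. The randomised real-versus-sham contrast, with one profile per person, is unaffected, and so is the primary outcome. The change is worth making because it costs very little, not because the trial's main conclusions depend on it.

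**What to change.** Add to Metabolomics study analysis:

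- The before/after contrast is fitted on within-person data, either by subtracting each participant's two-sample mean before PCA, PLS-DA or OPLS-DA (the multilevel form) or by modelling the week-4 minus baseline spectrum.
- Any cross-validation keeps both samples of a person together, and any permutation exchanges labels within person.
- Before/after tests of single metabolites use the paired t-test or Wilcoxon signed ranks test already named under Statistical analysis.
- The real-versus-sham contrast keeps the ordinary methods.

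The cost is a few sentences and one centring step before the data enter the same software, with no new samples or patients. The downside is that participants without a week-4 sample leave this one model. The text should say so, because the general rule of carrying the last observation forward would otherwise give such a person a pair with zero change.

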**Methods/design:**

We describe a proposal for a randomized, assessor-blind, sham-controlled trial with 70 eligible participants who will be randomly allocated either into an acupuncture or a sham group. Participants in the acupuncture group will receive 10 sessions of real acupuncture treatment and those in the sham group will be treated with identical sessions using a Streitberger needle. Functional magnetic resonance imaging (fMRI) and metabolomics studies will be implemented before and after 4 weeks of treatment to investigate the mechanism of acupuncture. The primary outcome is a proportion of responders with adequate symptom relief and the secondary outcomes include the Nepean Dyspepsia Index - Korean version, Functional Dyspepsia-Related Quality of Life questionnaire, Ways of Coping Questionnaire, Coping Strategies Questionnaire, perception of bodily sensation questionnaire, State-Trait Anxiety Inventory, and the Center for Epidemiological Studies - Depression Scale. The outcomes will be evaluated before and after the treatment.

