#### Inclusion criteria

The inclusion criteria are as follows:Age between 30 and 49 years.Meeting the definition of FD and postprandial distress syndrome (PDS) as a subtype of FD according to the Rome III criteria [17].Complaints of a degree of dyspepsia that produces a score of more than 40 points on the visual analog scale (VAS; 0, no symptom at all; 100, the most severe symptom one has ever had).Answer at least three questions worth more than 2 points on the Gastrointestinal Impact Scale.Have normal esophagogastroduodenoscopy results within a year and no evidence of any organic diseases.Individuals who are not supposed to take any other treatments associated with FD during the study.

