Current neuroscience studies using positron emission tomography-computed tomography on FD have demonstrated an association with the cerebral cortex. The anterior cingulate cortex (ACC), insula, and thalamus/hypothalamus, which are the key regions of “gut-brain communication,” might be most closely related to the severity of FD [52]. A recent report revealed that acupuncture might affect the activity of somatic and visceral sensation and therefore modulate the insula, ACC, and hypothalamus, which are related to the regulation of homeostasis [10]. One previous neuroimaging study reported a central mechanism of acupuncture associated with the pain and anxiety regions of the brain after gastric distension was induced by inserting a rubber balloon into the subjects’ stomach [53]. However, the methods of inducing gastric distension were considered to be inappropriate because they were inconvenient and invasive, and there was no intervention, such as acupuncture. Our study is the first neuroimaging study to focus on the potential central mechanism of real and non-penetrating sham acupuncture treatments for FD. We will investigate the associations between the clinical efficacy of acupuncture and the brain’s response to determine any differences with those of the sham acupuncture procedure. Additionally, our study is the first trial to focus on the methods of inducing abdominal discomfort experimentally by MA and a meal. As visceral hypersensitivity is one of the major mechanisms for PDS [54], we will investigate the central mechanism of hypersensitivity using fMRI and the mechanism of how acupuncture reduces MA-induced abdominal discomfort in both short-term and longitudinal periods.

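### The metabolomics contrasts can identify metabolites related to time or treatment but not markers of FD, and the named models in ordinary form ignore the pairing of baseline and week-4 samples

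*Protocol article*

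**What the plan says.** All statements are in the Protocol article.

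- **Population.** Inclusion criteria: "Meeting the definition of FD and postprandial distress syndrome (PDS) as a subtype of FD according to the Rome III criteria".
- **Arms.** Abstract, Methods/design: "70 eligible participants who will be randomly allocated either into an acupuncture or a sham group". The Discussion repeats 35 per group for the metabolomics. No non-FD group is planned. Healthy controls appear only in the Discussion's account of an earlier metabolomic study.
- **Contrasts.** The Metabolomics section lists them as "1) FD before and after acupuncture treatment and (2) the acupuncture and sham acupuncture groups", with blood and urine taken at baseline and after 4 weeks.
- **Product.** The same section says that "the patterns and biomarkers for FD could be discovered using a multivariate statistical analysis".
- **Methods.** Metabolomics study analysis names PCA first and continues that "partial least squares-discriminant analysis (PLS-DA), or orthogonal projections to latent structure-discriminant analysis (OPLS-DA) will be used to process the data". To find the variables behind group differences, "the loading plot, S-plot, or the variable influence on projection (VIP) value will be used".
- **Objective.** The third aim under Objectives is to relate metabolite differences and changes to clinical outcomes.

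**The concern.** A marker of FD is a metabolite whose level differs between people with and without FD. To find one, the data must contain both kinds of people. Here they contain only one, so the stated product does not match the design. A metabolite that moves over four weeks, or that differs between arms, could be reported as an FD marker when it shows only a time or treatment effect.

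The second issue is the match between objective and analysis. The objective is about change within participants. The named methods summarise or classify samples. Applied in ordinary form to before/after samples, they take no account of two samples coming from the same person, and nothing in the metabolomics analysis section makes change the quantity analysed.

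**Working it through.** **1. What each contrast can identify**

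| Contrast | What differs between the sides | FD at enrolment | Identifiable |
|---|---|---|---|
| Before vs after acupuncture | Treatment and everything else that changes over 4 weeks | Yes on both sides | Change over time |
| Acupuncture vs sham | Randomised treatment | Yes on both sides | Treatment-related difference |

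Let D = 1 for FD. D = 1 for all 70 participants, so Var(D) = 0 and no association with D can be estimated. This follows from who is enrolled. An analysis plan that is not shown could not alter it.

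**2. The plan's own figure**

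The only computable figure bearing on the metabolomics is the group size. From Sample size calculation: p_t = 0.70, p_c = 0.35, α = 0.05 two-sided, power 0.80, dropout 10%. The mean proportion is (0.70 + 0.35)/2 = 0.525.

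n = (1.960 × √(2 × 0.525 × 0.475) + 0.8416 × √(0.21 + 0.2275))² / 0.35²
= (1.384 + 0.557)² / 0.1225 = 30.75, so 31 per arm.

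31/0.90 = 34.4, so 35 per arm and 70 in total. This matches the plan. The figure was set for the responder proportion, and it is used below as the metabolomics group size.

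**3. Pairing**

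Take one metabolite with standard deviation σ at each visit, baseline-to-week-4 correlation ρ, and n participants per arm.

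- Before/after within an arm: ignoring pairing, the variance of the mean difference is taken as 2σ²/n. The correct value is 2σ²(1 − ρ)/n. With positive ρ, the unpaired analysis overstates the noise and loses sensitivity.
- Between arms: week 4 alone has variance 2σ²/n, change has 4σ²(1 − ρ)/n, and baseline-adjusted week 4 has about 2σ²(1 − ρ²)/n.
- Change beats week 4 alone only if 2(1 − ρ) < 1, that is ρ > 0.5. Baseline adjustment is never worse than either, because 1 − ρ² ≤ 1 and (1 − ρ)(1 + ρ) ≤ 2(1 − ρ).

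The article gives no ρ, so no numerical gain is claimed.

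**4. Why a validation check matters at this size**

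PLS-DA was fitted to independent Gaussian noise with group labels unrelated to the data, 35 per group, autoscaled, 1 to 3 components, 100 replicates per setting. The article does not give the number of spectral variables; 50, 200 and 1,000 are assumptions. The ranges below are setting means over 1 to 3 components.

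| Variables (assumed) | In-sample accuracy | In-sample R² | 7-fold cross-validated accuracy |
|---|---|---|---|
| 50 | 80–91% | 0.42–0.64 | 48–51% |
| 200 | 96–100% | 0.76–0.98 | 50% |
| 1,000 | 100% | 0.94–1.00 | 47–48% |

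Cross-validated Q² averaged between −0.94 and −0.08. It exceeded 0.5 in none of the 100 replicates in any setting, but exceeded 0 in up to 17%, so a bare Q² > 0 rule is weak. Results at 31 per group, close to the number left after 10% dropout, were similar. OPLS-DA, S-plots and correlated variables were not simulated.

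**The case against.** Much of the other side's case stands.

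- **The biomarker wording is hedged.** The text says could, not will, and neither Objectives nor Hypothesis claims a diagnostic marker. This is correct, and it is why the repair is small. The phrase could also be read loosely as markers of response among FD patients. But a metabolite that tracks symptom relief within patients is a response marker, and the text should say so.
- **PCA is listed first and uses no group labels; VIP is one of three tools.** True. S-plots and VIP do come from label-fitted models, however, and ordinary PCA does not account for pairing either.
- **The Statistical analysis section has paired tests for before/after continuous variables.** These may be meant for individual metabolites too. But the metabolomics section names only the multivariate methods, and a paired test within one arm does not compare change between arms.

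Two stronger readings are tempting, and the documents do not support them.

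- **That the plan will return biomarkers from pure noise.** This needs both an absence of validation and a selection cut-off. The article does not say validation will be omitted. Its silence on cross-validation, permutation and false-discovery control is ordinary for a condensed article. It gives no VIP threshold, and the result depends on one: at 35 per group, the share of noise variables flagged was 32–36% at VIP > 1, 10–14% at > 1.5 and 2–5% at > 2. That mean squared VIP equals 1 rules out every variable lying below 1; it does not by itself make many exceed 1.
- **That the hypersensitivity aim fails for the same reason.** The Discussion says "we will investigate the central mechanism of hypersensitivity using fMRI". That is an fMRI aim using individually calibrated pressure in FD patients, and it makes no patient-versus-normal claim. The lack of a non-FD group does not defeat it.

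**Conclusion.** The mismatch between the stated product and the design is certain from the document alone: with FD in all 70 participants and no contrast on FD status, markers of FD are not identifiable. The mismatch between a change objective and models that in ordinary form ignore pairing is a weaker point, because a fuller plan may use a paired version.

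The noise result supports a precaution and is not evidence of an error in the plan. It rests on assumed variable counts, independent noise and PLS-DA only. The metabolomics is a mechanistic secondary aim, and the responder analysis and trial sample size are untouched. This should be corrected, mostly by rewording.

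**What to change.** 1. In the Metabolomics section, replace the FD-biomarker wording with *metabolites that change with treatment*, labelled exploratory.
2. In Metabolomics study analysis, make the lead analysis a between-arm comparison of within-subject change (week 4 minus baseline) or of week-4 values adjusted for baseline. Adjustment is the safer choice where ρ is unknown. Either gives one record per participant, which removes the pairing problem and serves the third objective directly.
3. State that VIP values and S-plots only rank variables, and are read only after the model passes a label-permutation or cross-validation check. If the full plan already says this, a cross-reference is enough. If before/after samples are still modelled together, keep both samples from a person in the same fold and permute labels within person.

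The cost is a few sentences, slightly more analysis work and probably fewer reportable metabolites. No extra participants or samples are needed. Keeping a claim about FD markers would instead require a non-FD comparator, which is a change of design.
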